## METHODS/DESIGN

2

This protocol is based on Standard Protocol Items: Recommendations for Interventional Trials (SPIRIT) guidelines (Chan et al., 2013). (Additional file 1).

### Study setting

2.1

This school‐based trial will be conducted in Sari city, the capital of Mazandaran province, northern Iran. This city consists of two urban districts and both of them have a separate Department of Education. In the Iranian educational system, schools divided into two main categories, Public schools (free) and Private schools (tuition). In this city, the majority of the high school students educated in public schools, and just about 19% of them study in private schools (Statistical Centre of Iran, 2016). This study will be conducted on students in public high schools from both districts in Sari city.

### Study design

2.2

This study is a three‐armed parallel‐group non‐masked clinical trial, with two intervention groups named intervention group 1 (IG1), intervention group2 (IG2) and comparison group (CG). For prevention of contamination bias, school allocation to different arms will be random. Also, selection of students from the total eligible students in each school for participation in IGs and CG will be random. Outcomes assessment in IGs will occur at baseline (T0) and at the end of intervention as well as its equivalent in the comparison group (T1). After baseline assessment, the participants will be informed of which group they are assigned to.

### Inclusion and exclusion criteria

2.3

The main target group is 11th‐grade public high school students who have completed a written informed consent form by themselves and their parents/guardians before the study begins. Inclusion criteria include (a) single; (b) moderate to severe PMS according to the Premenstrual Syndrome Screening Tool (PSST); (c) regular menstrual periods (21–35 days); and (d) not a professional athlete. Exclusion criteria include (a) use of therapies due to PMS, at baseline and during the study; (b) hormonal or psychiatric drug intake affecting PMS, at baseline and during the study; (c) diagnosis of a chronic disease; and (4) occurrence of unfortunate/stressful events for adolescents or their family in the last 6 months and during the study.

### Intervention

2.4

In this study, the following steps will be implemented (Figure 1):

Schools will be purposefully selected from total schools in urban districts in Sari city;In each school, inclusion criteria will be assessed, including screening for moderate and severe PMS by PSST;After baseline assessment schools will be, randomly, allocated to one of three study arms: (a) Peer‐group education (IG1); (b) Health practitioner education (IG2); (c) comparison group (CG)All participants will be instructed to fill out the DRSP for two consecutive menstrual cycles;Re‐evaluation of exclusion criteria;Volunteer eligible students will be purposefully selected as peer educators and educated by the principal investigator (PI);The required sample for receiving interventions or participate as CG will be based on the random selection from the total eligible students in each school;Trained peer educators will implement the intervention in IG1;At the same time, the health practitioner will implement the intervention in IG2.

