### Recruitment and randomization

2.6

Three high population public secondary high schools in both districts in Sari city will be selected purposefully. In each school, all 11th‐grade students will fill out the socio‐demographic menstrual characteristics checklist, GHQ‐28 Items, and PSST which is a retrospective questionnaire to screen eligible participants. After that, schools will be randomly allocated to one of three study arms: (a) Peer‐group education (IG1); (b) Health practitioner education (IG2); (c) Comparison Group (CG) by using a random number table. Following recruitment and verification of study eligibility, required sample size (30 students in each group) will be selected randomly by a random allocation sequence generating using the built‐in random number generator in Microsoft Excel (Cheusheva, 2020). They will complete the DRSP (during two consecutive menstrual cycles). Before random sampling, ten volunteer students will be selected as peer educators purposefully and will be trained by the PI. At the end of the final session, the PI will select six students as peer educators by assistance of school staff. Since the intervention is educational, it will not be possible to design a blind study. The students who meet the inclusion criteria will be informed completely about the protocol of the study.

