#### Daily record of severity of problems (DRSP)

2.9.3

Change in the PMS severity as a primary outcome is measured by the DRSP in three groups over time. The PMS severity will be prospectively evaluated in two‐time points, at baseline (T0) and after the intervention (T1) for two consecutive months (Mirghafourvand et al., 2015). The standard reference for PMS diagnosis based on the two cycles of DRSP charting is as follows: The luteal phase is defined as the 7 days before menses and the follicular phase as the 6 days after the onset of menses (Borenstein et al., 2007). The DRSP questionnaire developed by Endicott et al. and is a standard tool for determining the severity of PMS. It divided premenstrual symptoms according to DSM‐5 criteria into five areas: depression, anxiety, emotional, retention and physical symptoms (Epperson et al., 2012). This tool consists of 24 items (21 symptoms items and 3 dysfunctional items) and ranked from 0 (not at all) to 3 (extreme) (Endicott et al., 2006). The total score, from 7 days before until 4 days after period adds together and divided to the days' which incidence symptoms; in this way, we will calculate the mean severity of symptoms. This questionnaire's validity (by ten experts) and reliability (by test‐retest method) have been approved (Sharifi et al., 2014).

The PMDD will be assessed by the PSST which is the useful tool for DSM‐V PMDD. The PMDD causes severe irritability, depression or anxiety in a week before the period starts and usually goes away two to four days after the period starts (Biggs & Demuth, 2011). It will be assessed in two points, at baseline (T0) and at the end of two menstrual cycles after the intervention (T1).

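### Sections 2.4 and 2.6 both allocate schools before the baseline DRSP is charted, and they contradict each other on whether sampling and peer training come before it

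*Protocol article*

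**What the plan says.** - **Primary outcome (2.9.3).** "Change in the PMS severity as a primary outcome is measured by the DRSP in three groups over time", assessed "at baseline (T0) and after the intervention (T1) for two consecutive months". The T0 DRSP is therefore the baseline of the primary outcome. Section 2.10 compares the three groups by ANCOVA adjusted for baseline values.
- **Section 2.4.** "After baseline assessment schools will be, randomly, allocated to one of three study arms". The next listed step is "All participants will be instructed to fill out the DRSP for two consecutive menstrual cycles". After that come the re-check of exclusion criteria, the selection and training of peer educators, the random draw of the required sample, and the intervention.
- **Section 2.6.** All 11th-grade students complete the checklist, GHQ-28 and PSST. Schools are then allocated. Thirty students per group are drawn at random, and the text continues "They will complete the DRSP (during two consecutive menstrual cycles"). The next sentence steps back in time: "Before random sampling, ten volunteer students will be selected as peer educators purposefully and will be trained by the PI".
- **Section 2.2.** "After baseline assessment, the participants will be informed of which group they are assigned to".
- **Table 1.** T0 occupies months 1–4. Recruitment and intervention occupy months 5–6.

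**The concern.** A baseline covariate protects a comparison only if the arm cannot have affected it. Here the one baseline that matters for the primary analysis is charted over two cycles that both sections place after the schools' arms are fixed. The trial is unmasked, a whole school shares one arm, and the students rate their own symptoms.

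Three things follow.

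1. The assessment that 2.4 places before allocation does not include the baseline of the primary outcome.
2. The exclusion re-check also falls after allocation, so the eligible pool can come to differ by arm for reasons other than chance.
3. Under the order in 2.6, training on PMS and how to manage it could reach students in the peer-education school before that school's baseline is charted. A shift confined to that arm would also distort the peer-versus-practitioner contrast, which is the primary objective.

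**Working it through.** **1. The plan's own figure.** Section 2.5 uses a standardised effect of 0.8, z values of 1.96 and 0.84, and n = 2 × (1.96 + 0.84)² / 0.8² = 2 × 7.84 / 0.64 = 24.5, rounded up to 25 per group. This reproduces. The point does not change it; 0.8 SD serves below only as the yardstick.

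**2. The two orders side by side.**

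| Order | Section 2.4 | Section 2.6 |
|---|---|---|
| 1 | PSST screening and other criteria | Checklist, GHQ-28, PSST |
| 2 | Schools allocated | Schools allocated |
| 3 | DRSP, two cycles, all participants | Peer educators selected and trained |
| 4 | Exclusion re-check | Random draw of 30 per group |
| 5 | Peer educators selected and trained | DRSP, two cycles, those drawn |
| 6 | Random draw | Intervention |
| 7 | Intervention | – |

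The sections agree that allocation precedes the DRSP. They contradict each other on sampling and on peer training, both of which come after the DRSP in 2.4 and before it in 2.6.

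**3. Whether Table 1 settles it.** Inputs: cycles of 21–35 days (2.3), peer training over 3 weeks (2.4.1), intervention over 3 weeks (2.4.2, 2.4.3), and a month taken as 30.4 days.

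- Two cycles last 2 × 21 = 42 to 2 × 35 = 70 days. Adding 21 days of peer training gives 63–91 days, which fits inside months 1–4 (4 × 30.4 ≈ 122 days). The 2.6 order is feasible.
- Peer training plus intervention lasts 21 + 21 = 42 days, which fits inside months 5–6 (2 × 30.4 ≈ 61 days). The 2.4 order is feasible.

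Table 1 is compatible with both.

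**4. What a shifted baseline would do.** Let X be the undisturbed baseline in SD units, G = 1 in the affected arm, b the ANCOVA slope of T1 on T0, and d the amount by which the arm lowers the recorded baseline. Take a true T1 difference of −0.8:

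- T1 = bX − 0.8G + error
- recorded T0 = X − dG, so X = T0 + dG
- T1 = b·T0 + (−0.8 + bd)G + error

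The estimated reduction is 0.8 − bd. The documents give neither b nor d, so both are assumptions. Each cell shows the bias in SD and as a percentage of 0.8:

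| Slope b | d = 0.1 | d = 0.2 | d = 0.4 |
|---|---|---|---|
| 0.3 | 0.03 (3.8%) | 0.06 (7.5%) | 0.12 (15%) |
| 0.5 | 0.05 (6.3%) | 0.10 (12.5%) | 0.20 (25%) |
| 0.7 | 0.07 (8.8%) | 0.14 (17.5%) | 0.28 (35%) |

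A true reduction of 0.80 SD would appear as 0.77 down to 0.52 SD. A simulation with 30 per arm, b = 0.5, d = 0.2 and 5,000 repetitions gave a mean of 0.700, as the formula predicts (0.80 − 0.10). A baseline raised rather than lowered in one arm would bias the contrast by the same amount in the other direction.

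**The case against.** The strongest reply is section 2.2. Participants learn their group only after baseline assessment, the sentence before it defines that assessment as T0, and 2.9.3 makes the DRSP a T0 measure. Read together, students would chart the DRSP without knowing their arm. This carries weight and lowers the risk. It does not close the point, because 2.4 uses the same term for the stage before allocation, which cannot include the DRSP. Disclosure might therefore come before charting. The sentence also covers participants only, and visible peer training could reveal the arm.

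The second reply is that 2.6 is not strictly chronological. A reader might infer that six sessions on PMS are certain to run in the peer-education school before its baseline. The documents do not support that. No sentence places the training before the DRSP; it follows only if the sampling-then-DRSP order in 2.6 is taken literally, and 2.4 says the reverse. That peer educators come only from that school is implied, not stated.

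Third, a reader might infer that people who know the arm carry out the exclusion re-check. Section 2.4 does not say who does it. Under the 2.4 order those exclusions also precede the draw of the 30, so they are not losses from the sampled group, although they can still shape the pool it is drawn from.

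Last, Figure 1 is not available here and may show the intended order. It would not remove the contradiction between the two sections' text.

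**Conclusion.** The point stands as a design weakness with an internal contradiction. Allocation before the primary baseline is stated in both sections, and the conflict over sampling and peer training is plain on the text. Neither section 2.2 nor Table 1 resolves it.

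The conclusion is that the baseline and the exclusion re-check **can** be influenced by arm. The documents do not show that they are. The 0.03–0.28 SD range (about 4–35% of the planned effect) is purely illustrative: it depends on assumed slopes and shifts, and on a shift confined to one arm. The upper end assumes that incidental exposure yields half the planned effect (0.4 of 0.8 SD). It should not be cited as an estimate of bias. The change is worth making because it removes this source of bias without altering the sample size.

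**What to change.** State one order, the same in 2.2, 2.4 and 2.6:

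1. screening with the checklist, GHQ-28 and PSST;
2. two T0 DRSP cycles in all three schools;
3. exclusion re-check completed and the list of eligible students locked;
4. random allocation of schools;
5. disclosure of the arm, then selection and training of peer educators;
6. random draw of 30 students per school from the locked list.

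Say in 2.2 that baseline assessment includes both DRSP cycles.

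The article reports a launch on 4 April 2020 with recruitment still open, so schools may already be allocated. In that case, state the order actually used, complete the DRSP before disclosure and peer training wherever that is still possible, and report post-allocation exclusions by arm.

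**Cost.** If allocation has not yet happened, this is re-ordering only: Table 1 already places T0 in months 1–4, ahead of the intervention. The downside is that some students not later drawn will have kept DRSP charts, which 2.4 already implies. If allocation has happened, the cost is a short clarification and one extra tabulation, and the influence on the baseline can be limited but no longer ruled out by design.

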**FIGURE 1 nop2858-fig-0001:**
[figure not shown]
Study enrolment, allocation and intervention flow diagram

#### Training of peer educators

2.4.1

At first, ten eligible volunteer students will be selected as potential peer educators to educate their peers. They will educate about life skills (include problem‐solving, critical thinking, effective communication skills, decision‐making, creative thinking, interpersonal relationship skills, self‐awareness building skills, empathy and coping with stress and emotions), puberty, menarche, physiology of menstruation, PMS, and its management (such as dietary changes and the use of aerobic exercise) by PI during six face‐to‐face 60‐min sessions, in 3 weeks (twice a week). In the following, six of them who are qualified from school staff as well as PI's point of view will be select as peer educators to implement the intervention. The PI is a Master of Science degree student in midwifery counselling.

##### Preference will be given to students who have demonstrated the following

Assisting and contributing to a positive peer‐to‐peer environment;Have a history of student leadership/working with peers/groups in school;Enthusiasm and commitment for working on a team and interest in health topics;Ability to have effective communication skills, active listening, empathy, confidentiality, non‐judgmental listening and altruism;Availability to attend Peer Educator Training and meetings are mandatory.

#### Peer‐group education

2.4.2

Participants in this group (IG1, *n* = 30, three subgroups with ten members) educated by two peer educators in each subgroup in six‐60‐min sessions for 3 weeks (twice a week) which will be supervised by the PI. The sessions will be in form of online in WhatsApp application and include voice records, audio PowerPoint, short video clips, educational pamphlets, and at the end of every session, sometime will be dedicated to question and answer. The content of sessions will include issues like puberty, menarche and menstrual cycles, PMS and its management.

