#### Health practitioner education

2.4.3

Simultaneously with the peer‐group education, participants in IG2 (*N* = 30) will be educated by a health practitioner in six‐60‐min sessions for 3 weeks (twice a week). The content and delivery route of each session will be similar in two intervention groups.

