### Sample size

2.5

Sample size will be determined at CI: 95% and Power: 80%, Large Cohen effect size = 0.8, in the intervention group, compared to the control group, and by the assistance of following formula:
$$n=\frac{2*{\left(z1‐\frac{\alpha }{2}+z1‐\beta \right)}^{2}}{E{\text{.S}}^{2}}=\frac{2*{\left(1.96+0.84\right)}^{2}}{{\left(0.8\right)}^{2}}=25.$$
z0.975=1.96z0.8=0.84.

By considering an attrition rate 25%, the sample size in each group will be calculated, 30 students.

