### Statistical analysis

2.10

All analyses of the outcomes will performed as intention‐to‐treat analyses and following the TREND checklist. The normality of distribution will be examined by the Kolmogorov–Smirnov test. All quantitative variables will be expressed as mean ± *SD*. Categorical variables will be presented as frequencies and percentages. The chi‐square test will be used to test for differences between categorical variables. Baseline means differences will be tested using a one‐way analysis of variance (ANOVA or the non‐parametric equivalent of that Kruskal–Wallis). Analysis of covariance (ANCOVA) will be used to identify differences between the three groups at the end of the study, adjusting for baseline values and covariates. The comparison of mean values will be conducted within groups after the intervention period using paired sample *t* tests. *p* < .05 will be considered statistically significant. Statistical tests of the outcome measures will be performed using Statistical Package for the Social Sciences (SPSS version 18.0).

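### IG1 is taught in three peer-led subgroups, but the sample size and the ANCOVA treat its students as independent, so any positive subgroup correlation makes the IG1 standard errors too small

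*Protocol article*

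**What the plan says.** Section 2.4.2 (Peer-group education) sets IG1 at 30 students in "three subgroups with ten members) educated by two peer educators in each subgroup", with question time closing every session. Section 2.4.1 selects six peer educators, which makes three pairs for three subgroups. Section 2.4.3 says the 30 students of IG2 "will be educated by a health practitioner in six" sessions of an hour and mentions no subgroups. Section 2.4.4 gives the comparison group (CG) the usual school counselling only.

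Section 2.5 sizes the trial as two independent samples, an intervention arm against the control arm: "Sample size will be determined at CI: 95% and Power: 80%, Large Cohen effect size = 0.8". It reaches 25 per group and then 30: "By considering an attrition rate 25%, the sample size in each group will be calculated, 30 students". No ICC or design effect appears.

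Section 2.10 names the outcome model: "Analysis of covariance (ANCOVA) will be used to identify differences between the three groups at the end of the study, adjusting for baseline values". Adjustment for covariates is planned as well. No subgroup or school term is named. Section 2.6 allocates three schools to three arms, so each arm is one school.

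**The concern.** Students in one IG1 subgroup share the same two educators and the same discussion. If one pair teaches better than another, the T1 scores of its ten students move together. The study creates no such groups in CG and states none for IG2, so the design is partially nested: IG1 carries a source of variance that neither the formula nor the ANCOVA recognises.

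This correlation comes from how IG1 is delivered. It would be there even if students had been randomised individually.

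IG1 enters both main hypotheses in section 1.1, and the intended conclusion is that peers can stand in for practitioners. That generalises from three pairs to peer educators as a class, so variation between pairs belongs in the error term. If it is left out, an unusually good or poor pair can be read as an effect of peer education, with an interval that is too narrow.

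**Working it through.** **Inputs from the protocol.** Two-sided 5% level (1.96), 80% power (0.84), standardised difference 0.8, 25% attrition, 30 per arm (2.5); three IG1 subgroups of ten (2.4.2).

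**Assumption.** The protocol gives no subgroup ICC. Values of 0.01, 0.05 and 0.10 are used.

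**The plan's own figure.** n = 2(1.96 + 0.84)² / 0.8² = 24.5, rounded up to 25. This reproduces the stated number. Power at 25 is Φ(0.8/√(2/25) − 1.96) = 80.7%, for independent students.

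**SE of IG1 minus CG.** With n per arm, subgroup size m and SD 1:

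SE = √{[1 + (m − 1)·ICC]/n + 1/n}

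At n = 30, m = 10, ICC 0.05 the IG1 design effect is 1 + 9 × 0.05 = 1.45. SE = √(1.45/30 + 1/30) = 0.286, against √(2/30) = 0.258 under independence, a ratio of 1.107. The false-positive rate of the plain test is approximately 2[1 − Φ(1.96/ratio)].

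| ICC | IG1 design effect | True SE / plain SE | False-positive rate |
|---|---|---|---|
| 0 | 1.00 | 1.00 | 5.0% |
| 0.01 | 1.09 | 1.02 | 5.5% |
| 0.05 | 1.45 | 1.11 | 7.7% |
| 0.10 | 1.90 | 1.20 | 10.4% |

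Simulating a pooled t test with 30 per arm gives 5.4%, 7.6% and 10.6% at the three positive ICCs, in agreement.

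**Unadjusted power for IG1 versus CG at d = 0.8,** normal approximation Φ(0.8/SE − 1.96), with m = n/3:

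| ICC | 30 analysed | 25 analysed | 22.5 analysed |
|---|---|---|---|
| 0 | 87.3% | 80.7% | 76.5% |
| 0.01 | 85.8% | 79.3% | 75.2% |
| 0.05 | 79.9% | 73.9% | 70.2% |
| 0.10 | 73.0% | 67.7% | 64.5% |

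The last column is what the plan's own attrition leaves: 30 × 0.75 = 22.5. Keeping 25 after a 25% loss needs 25/0.75 = 33.3, so 34 enrolled. The 76.5% at ICC 0 is therefore an attrition shortfall and owes nothing to clustering.

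**Small-sample degrees of freedom.** The normal approximation is optimistic with three subgroups. A simulated test on the three subgroup means with Satterthwaite degrees of freedom, 25 analysed per arm, has about 58% power at ICC 0.05.

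**Can three subgroups estimate the ICC?** The between-subgroup variance estimate is zero when the between mean square falls below the within one. With k = (1 + 9·ICC)/(1 − ICC), the probability is P(F(2,27) < 1/k): about 58%, 47% and 37% at ICC 0.01, 0.05 and 0.10.

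**The case against.** **The size rests on an assumed ICC.** This stands. Much of the teaching material is packaged (recordings, slides, clips, pamphlets) and supervised by the principal investigator, which may keep the correlation low. At ICC 0.01 the power loss with 25 analysed is 1.4 points (80.7% to 79.3%) and the error rate is about 5.5%.

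**A reader might infer that the stated 80% power is simply not delivered.** The documents do not support that. With all 30 retained, unadjusted power is still about 80% at ICC 0.05. The planned test also adjusts for baseline. If the baseline correlation were 0.5 (an assumption) and baseline explained only within-subgroup variance, power at ICC 0.05 with 25 analysed would be about 83%. Here the residual variance is 0.75 and the residual ICC 0.05/0.75 = 0.067, so SE = √{0.75 × (1.489 + 1)/25} = 0.273 and Φ(0.8/0.273 − 1.96) ≈ 0.83. The same adjustment does not correct the SE: with m = 10 the ratio of true to plain SE would rise from 1.11 to 1.14.

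**One school per arm is the larger problem.** This stands too. School variance cannot be separated from arm and enters every contrast; CG students share a school and its counsellor, and IG2 students share a practitioner. An SE corrected for subgroups is therefore still not a full SE, and calling it one would give false reassurance. That does not remove the subgroup issue, which has a different cause.

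**A subgroup term is a detail for an analysis plan.** This does not stand as a full answer. The article prints the formula and names the model, and both conflict with the delivery structure it fixes.

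**Conclusion.** The point holds in conditional form. The stated formula and model ignore a grouping that the protocol itself creates in IG1, so the SEs of the IG1 contrasts are too small at any positive ICC. Over an assumed ICC of 0.01 to 0.10, the true IG1-versus-CG SE is about 2% to 20% larger than the plain one, and the false-positive rate is about 5.5% to 10.4%.

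The 80% power in section 2.5 holds only for independent students. Whether power actually falls below 80% depends on the ICC, on retention and on the baseline correlation, none of which the documents settle beyond the 25% attrition figure. The IG1-versus-IG2 contrast is affected in the same direction; IG2 versus CG is not affected by the IG1 subgroups.

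**What to change.** **Conduct (2.4.2 and 2.6).** Record each IG1 student's subgroup, and assign the 30 students to the three subgroups at random.

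**Analysis (2.10).** Beside the plain ANCOVA, report the baseline-adjusted IG1 contrasts with the IG1 variance inflated at prespecified ICCs of 0.01, 0.05 and 0.10. Keep a partially nested mixed model (random subgroup effect in IG1 only, small-sample degrees of freedom) as supportive. It should not be the main analysis, because three subgroups cannot estimate the ICC reliably.

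**Sample size (2.5).** State that 80% power assumes independent students. Give the conditional range at ICC 0.01, 0.05 and 0.10: 79%, 74% and 68% with 25 analysed; 75%, 70% and 64% with 22.5. Label these as unadjusted normal approximations, and add that a test with small-sample degrees of freedom on three subgroups has clearly lower power (about 58% at ICC 0.05 with 25 analysed).

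**Limitation.** Say that none of this addresses one school per arm.

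**Cost.** Wording in two sections, one extra variable and a simple random split; no extra students or staff. The downside is wider IG1 intervals and a less favourable stated power.
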